**Methods/Design:**

The study participants will be 115 youth ages 8-15 y (45 with the syndrome and 70 without the syndrome but categorized as obese). The study will use a parallel design with the control group receiving the intervention after serving as control. Participants will be expected to complete a physical activity curriculum 4 days a week for 6 months including playground games 2 days a week and interactive console games 2 days a week. Parents will be trained at baseline and then provided with a curriculum and equipment to guide their implementation of the program. Tips related to scheduling and coping with barriers to daily program implementation will be provided. Throughout, parents will be contacted by phone once a week (weeks 1-4) and then every other week to receive support in between visits. Measurements of children and parents will be obtained at baseline, 12 weeks, and at the end (week 24) of the intervention. Children main outcomes include physical activity (accelerometry), body composition (dual x-ray absorptiometry), motor proficiency (Bruininks-Oseretsky Test of Motor Proficiency), quality of life and physical activity self-efficacy (questionnaires). Intervention compliance will be monitored using mail-in daily self-report checklists.

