## Methods/Design

### Study design

The Active Play @ Home study will evaluate the effectiveness of a 24-week PA intervention on select motor and health–related parameters in children with PWS and children with obesity but without PWS. The study has a quasi-experimental design with semi-random assignment to an intervention group or a wait-listed control group. The intervention group will consist of families with a child with PWS (n=35) and families with a child who is obese (n=50). Ten additional families with a child with PWS will be assigned to a wait-list control group and 20 families with an obese child without PWS will also serve as a wait-list group. Both wait-listed groups will serve as control groups prior to being enrolled in the PA intervention. Groups of two to four families will complete all baseline and follow-up testing on the same day throughout the study. The semi-random assignment consists of a priori established participant cohorts for both intervention and control groups. Upon recruitment, participants will be provided with tentative dates for their visits and their randomization to the cohort (intervention vs. control) will be based on their date preferences. Ethic committee approvals have been obtained from the California State University Fullerton Institutional Review Board and the United States Army Human Research Protection Office. During the first visit, after all study procedures are verbally explained, participants will have time to read the informed assent and consent forms and ask questions regarding the procedures. Afterwards, children participants will sign the informed assent form and their parents or guardians will sign the informed consent form. Figure 1 presents a timeline of the study procedures.

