### Data analyses

The main purpose of this study is to investigate short-term changes (immediately following the 24-week intervention) in PA, motor proficiency, and health-related outcomes in children with and without disability following completion of a physical activity program conducted in the home environment. A 2 (time: pre, post) by 2 (group: control, intervention) by 2 (youth: obese or PWS) mixed model ANOVA will be used to assess changes in the primary outcome (i.e., physical activity). Similar analyses will also be performed to assess changes in gross motor proficiency, body composition, and central sensory reception and integration. Other changes that will also be evaluated using mixed model ANOVAs include changes in quality of life, child self-efficacy, parent regulatory efficacy, and parent social influences. Potential confounders will serve as covariates where appropriate.

A power analysis was performed using G*Power 3.1.9 to identify the appropriate sample size for a power of .95, an alpha level of .05 and a correlation between time points was assumed to be .50. A small to moderate effect size (*f*=.20) was chosen, given the variability in physical activity expected in children with PWS [15]. A sample size of 84 was identified to provide sufficient power to detect an interaction. Given a 30% probability of drop-outs, 115 children will be recruited.

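### Recruiting 115 children does not leave the required 84 after 30% drop-out: about 80 are expected, and 120 recruits would be needed

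*Protocol article*

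**What the plan says.** Under Data analyses, the protocol article bases its sample size on "a power of .95, an alpha level of .05 and a correlation between time points was assumed to be .50", with an effect size of f = .20. It concludes: "A sample size of 84 was identified to provide sufficient power to detect an interaction". The next sentence goes from that requirement to the recruitment target: "Given a 30% probability of drop-outs, 115 children will be recruited".

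The target of 115 appears elsewhere too. The abstract (Methods/Design) splits it into 45 children with Prader-Willi Syndrome (PWS) and 70 with obesity. Study design splits it into an intervention arm of 35 + 50 = 85 and a wait-list control arm of 10 + 20 = 30. The article gives no other drop-out rate and no other route to 115.

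**The concern.** The sentence tells the reader that 115 was chosen so that enough children remain after 30% are lost. If 115 at 30% loss does not leave 84, the trial falls below its own requirement under its own attrition assumption, and the stated power of .95 does not apply to the number expected to be analysed. This is the sample-size justification for the primary outcome, so a reader will take it as evidence that attrition of that size has been covered.

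**Working it through.** **Inputs, all from the protocol article.** Required number 84, drop-out 30%, recruitment 115, f = .20, alpha .05, power .95, correlation between time points .50 (Data analyses). Cell sizes: 35 PWS and 50 obese in the intervention arm, 10 PWS and 20 obese in the control arm (Study design).

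**Step 1: reproduce the 84.** Take the within-between interaction with two time points and two equal groups. The noncentrality is λ = f² × N × m / (1 − ρ) = 0.04 × N × 2 / 0.50 = 0.16N, with 1 and N − 2 degrees of freedom.

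| N | λ | Power |
|---|---|---|
| 83 | 13.28 | .9496 |
| 84 | 13.44 | .952 |

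So 84 is exactly the smallest number that reaches .95. The base figure is sound on this model, and it has no slack.

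**Step 2: the drop-out step.**

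- Recruits needed to keep 84: 84 / (1 − 0.30) = 120.
- Completers expected from 115: 115 × 0.70 = 80.5.
- Largest loss that 115 can absorb: 1 − 84/115 = 27.0%.
- The common incorrect inflation: 84 × 1.30 = 109.2, or 110 rounded up.

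Neither the correct formula nor the usual mistake gives 115. The gap to 120 is 5 recruits, which is 5/115 = 4.3% of the target.

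**Step 3: power at the number expected to remain (same equal-group model).**

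| Completers | Power |
|---|---|
| 80 | .942 |
| 81 | .945 |
| 84 | .952 |

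**Step 4: power with the planned allocation.** This matters only for restating power correctly. Assume the same standardised difference and the same proportion lost in every cell.

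- Two arms at 85:30. λ is multiplied by 4 × 85 × 30 / 115² = 0.771.
- Four cells at 35, 50, 10 and 20, with the two populations weighted equally. λ is multiplied by (16/115) / (1/35 + 1/50 + 1/10 + 1/20) = 0.1391 / 0.1986 = 0.701, with N − 4 error degrees of freedom.

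| Completers | Equal groups | 85:30 | Four cells |
|---|---|---|---|
| 80 | .942 | .874 | .841 |
| 81 | .945 | .878 | .845 |
| 84 | .952 | .889 | .858 |

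Comparing 80 with 84 within each column, the drop-out error costs 1.0, 1.5 and 1.7 percentage points. The remaining difference from .95 comes from the allocation.

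**The case against.** The case on the other side accepts the arithmetic and disputes its weight.

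- *The effect is minor.* Power of .942 against a target of .95 threatens nothing, and no decision on design or analysis depends on it. This stands as a statement of size. It does not make the three figures consistent.
- *The .84 to .88 range belongs to another issue.* This is right: nearly all of that drop comes from the 85:30 split and would remain with 120 recruits in the same proportions. The range is relevant here only because a corrected power statement should describe the trial as it will be run.
- *The drop-out figure is a probability.* If each of 115 children has an independent 30% chance of dropping out, the number of completers has a standard deviation of √(115 × 0.30 × 0.70) = 4.9, so 84 or more could remain by chance. That is also true, and it is why the text should say about 80 expected. Planning still rests on the expectation, which is 80.5.
- *Rounding.* The authors may have called 27% roughly 30%, or set round cell sizes by what was feasible in a rare condition. Either is possible, but the article says neither, and it presents 115 as following from the 30%.

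**Conclusion.** The concern holds. The requirement of 84, the 30% loss and the target of 115 cannot all be right: 115 covers 27.0% attrition, and 30% would require 120. The shortfall at 30% is 3 to 4 expected completers. On its own it lowers power from .952 to about .94 under the plan's equal-group model with f = .20 and a correlation of .50. This is a wrong figure in the justification, not a serious loss of power. The further fall to about .84 to .88 is due mainly to the unequal allocation. It assumes the same standardised difference and proportional attrition across cells.

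**What to change.** Keep 115 and correct the sentence under Data analyses in one of two ways:

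1. State that 115 recruits allow for up to 27% drop-out while retaining 84 children.
2. State that 30% drop-out would leave about 80 analysable children, and give the power for that number under the actual allocation of 85 intervention to 30 control, with its assumptions.

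The second is more informative, because it also shows what the allocation does to power. Either costs one corrected statement and changes neither recruitment nor study procedures. Raising the target to 120 would also reconcile the figures, but that means five more families, and the size of the effect does not call for it.

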## Discussion

The Active Play @ Home study differs from other home-based intervention studies because it provides parents and children with a well-rounded and systematically progressed game-based curriculum. Additionally, the 24-week PA intervention is much longer than previous studies (i.e., 3-weeks to 3-months). Moreover, in terms of intervention programs designed for children with disability, this study is unique in that it is delivered in the home environment with parents or caregivers serving as agents of change. Moreover, the games and exercises can be modified for larger or smaller play spaces and indoor or outdoor environments using minimal playground equipment.

Social influences received from family have frequently been identified as playing a key role in children’s physical activity behavior [29]. We have developed a curriculum that requires active involvement of the parents in providing PA opportunities for their children. In families that have more than one child, the implementation of this curriculum can also benefit other children in the family. Moreover, all activities can be adapted to be played with more children, in which case neighbors, cousins, or friends can participate.

Children who have a rare disease may have less opportunity to participate in appropriate PA in a group setting. Sometimes their motor skills or their intellectual ability present a hurdle for such participation. Individual PA programs may promote PA in an appropriate manner. Several strategies using console-based games have been tested in different populations with disability suggesting promising results. However, strategies that include a game-based curriculum including both playground games and console-based games to be played in the home environment such as the one we have designed have yet to be tested. This type of strategy needs to tested as it could provide an alternative option to common after-school programs to increase physical activity in children with and without disability.

## Abbreviations

PA: Physical activity; PWS: Prader-Willi syndrome; BMI: Body mass index; DXA: Dual x-ray absorptiometry; BOT: Bruininks-Oseretsky test of motor proficiency; SOT: Sensory organization test.
